#### RQ2: What changes are observed in study outcomes at the single-case level during the Booster intervention?

Second, we will use the permutation distancing test (PDT) and single-case interrupted time series analysis (ITSA) to explore changes at the single-case level during the Booster intervention. The PDT will test the null hypothesis that observations within one individual are evenly distributed between Phase A and B. The PDT compares the observed test statistic (mean level change) to the test statistic distribution of permuted orders of observations. To create this distribution, the PDT uses different subsets of observations with a specific time distance to compensate for serial autocorrelation [53]. With the ITSA, a regression model is fitted to the data, allowing for separate intercepts and slopes in Phase A and B, while correcting for serial autocorrelation [54]. Although neither test can directly establish causality (e.g. the PDT was developed specifically for AB-phase SCODs) [53], together they complement the group-level SCRT results by identifying which individuals show significant change in outcomes in Phase B (responders) and which do not (non-responders). This triangulation approach leverages the strengths of both tests (e.g. the non-parametric PDT has no distributional assumptions, the ITSA enables trend analysis) and provides a comprehensive understanding of the data. In particular, the ITSA helps determine whether significant level changes found could be attributed to trends in the data instead of a possible intervention effect [54]. The combined results from both statistical tests strengthen the overall evidential basis, suggesting increased robustness and reliability of the findings.

#### RQ3: What is the pattern of change in the study outcomes at the single-case level?

We will conduct single-case change point analyses for participants in which significant changes in mean level or slope were detected by the PDT and/or ITSA (RQ2). Data will be analysed with Wild Binary Segmentation (WBS) [62]. WBS has no assumptions. It tests for change points by splitting the longitudinal observations into random intervals. Per individual, the analysis gives insight into the exact moment of change (both level and slope) for each outcome. This will provide us with information on which Booster intervention stages or elements were relevant to changes in the study outcomes across individuals. In the future, this information on effective intervention mechanisms could be used to improve the Booster intervention further.

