### Objectives {7}

The primary objective of the study is to examine the effect of the Booster intervention on FSE and the other study outcomes: fatigue severity, school participation, life satisfaction, and perceived health. Study outcomes will be evaluated at the group level (research question (RQ) 1) in adolescents (12 to 18 years) with a chronic health condition in a stable phase. Participants will have experienced hindrance by fatigue for at least 3 months. We hypothesise that FSE increases first, followed after four weeks by decreased fatigue severity, and after six weeks by improved school participation, life satisfaction, and perceived health.

The secondary objective is to gain insight into individual differences regarding (moment of) significant change in outcomes during the Booster intervention. At the single-case level, we will explore which participants show change in outcomes (RQ2) and when these responders start to show change (RQ3). In addition, at group level, we will study whether baseline participant characteristics are predictive of improvements during the Booster intervention (RQ4) and whether long-term change can be observed (RQ5).

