## Statistical methods

### Statistical methods for primary and secondary outcomes {20a}

#### RQ1: What is the effect of the Booster intervention on the study outcomes at the group level?

We will study change in mean level of outcomes (level change) after outcome-specific lags (Suppl. Figure 1). We hypothesise that FSE, Booster’s main target, will improve immediately after the Insight Conversation. Improvements in fatigue and participation are expected four weeks later, with life satisfaction and perceived health improving at six weeks post-Insight Conversation. After visual inspection of the data, the multiple baseline SCRT will determine the presence of significant medium to large Booster intervention effects at the group level. The null hypothesis is that observed outcomes are independent of intervention phase. The randomisation of intervention start is a precondition for conducting the SCRT. It tests significance by comparing the observed test statistic (mean level change) to the test statistic distribution of all other possible intervention start points. This controls for time-related confounding [60, 61]. The SCRT outcomes will show if the Booster intervention is effective at the group level.

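### RQ3 says Wild Binary Segmentation dates slope changes exactly, but the named method detects mean shifts only and dates gradual improvement about 1 to 5 weeks late, depending on how gradual it is

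*Protocol article*

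**What the plan says.** Under Statistical methods {20a}, RQ3, the protocol article analyses participants in whom "significant changes in mean level or slope were detected by the PDT and/or ITSA". ITSA fits separate slopes in the two phases (RQ2) and the gate is and/or, so a participant whose only finding is a slope change is admitted.

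One method is named for all of them: "Data will be analysed with Wild Binary Segmentation (WBS) [62]. WBS has no assumptions". Its output is described thus: "the analysis gives insight into the exact moment of change (both level and slope) for each outcome". The dates are then to show "which Booster intervention stages or elements were relevant to changes in the study outcomes".

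The Objectives {7} define the target of RQ3 as the time at which responders begin to change, which is an onset. The same section states the timing hypothesis: "FSE increases first, followed after four weeks by decreased fatigue severity". RQ1 repeats it relative to the Insight Conversation: "Improvements in fatigue and participation are expected four weeks later, with life satisfaction and perceived health improving at six weeks post-Insight Conversation".

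**The concern.** Standard WBS searches random sub-intervals of the series and, in each, looks for the day that best separates a lower mean from a higher one. Its reference model is a flat series and its alternative is a jump. A change of slope is not among its alternatives, so a ramp is approximated by one or more steps placed somewhere along it. This happens even with independent errors.

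Three consequences follow for RQ3.

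- The onset of a gradual improvement is reported late. Gradual change is plausible here, since goals are pursued over a twelve-week Experiment Period.
- A change that begins slowly in the Measurement Period may be dated after the Insight Conversation. Sample size {14} and the Discussion say that the change points are meant to show whether change already occurs in the Measurement Period.
- If one outcome jumps and another climbs slowly from the same day, the two dates differ although the onsets do not.

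The dates carry some weight. The Discussion says that single-case effects which align with specific stages help to build the case for efficacy, at effect sizes that the group-level test has limited power to detect.

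**Working it through.** **Inputs from the protocol.** Baseline 10 to 18 days; Measurement Period four weeks (28 days); Experiment Period twelve weeks (84 days); assumed autocorrelation 0.30; smallest effect detectable by the PDT 0.3 (Table 1). The stated 130 daily measurements are reproduced at the longest baseline: 18 + 28 + 84 = 130. The Insight Conversation then falls on day 46 (day 38 at the shortest baseline: 10 + 28).

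**Assumed, because the protocol does not give them.** Ramp length (14 to 84 days), a linear shape that then stays flat, total change (1 to 3 SD), and a WBS threshold of C·σ·√(2 log n) with C = 1.3, or C = 1.0 with σ scaled up for autocorrelation.

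**Step 1: where a single step lands on a noiseless ramp.** The best step sits where the signal equals the average of the two segment means. Take a ramp from day 46 to day 130 and let x be the days after onset. In units of the daily slope the left mean is x²/[2(46 + x)] and the right mean is (x + 84)/2. Then

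x = ½{x²/[2(46 + x)] + (x + 84)/2}, so (3x − 84)(46 + x) = x², so x² + 27x − 1932 = 0, so x = (−27 + √8457)/2 ≈ 32.5 days.

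For a 28-day ramp followed by a 56-day plateau, try x = 14. The left mean is 98/60 = 1.6, the right mean is (294 + 1568)/70 = 26.6, and their average is 14.1, so the step lands about 14 days after onset. A direct search over whole days, with onset on day 38, 42 or 46, gives 8 days late (14-day ramp), 15 (28-day), 21 to 22 (42-day), 27 to 28 (56-day) and 33 to 36 (84-day).

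**Step 2: WBS on noisy series.** Median days from true onset to the reported change point:

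| True course | 1.4 SD, onset day 42, C = 1.3 | 1 to 3 SD, onset day 46, autocorrelation 0.30: dominant change point |
|---|---|---|
| Step | 0 | 0 |
| 14-day ramp | 6–7 | 7–8 |
| 28-day ramp | 14–16 | 14–15 |
| 42-day ramp | 20 | 21–22 |
| 56-day ramp | 27–28 | 25–27 |
| 84-day ramp | 31–34 | 30–34 |

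Scatter is wide. For the 84-day ramp the interquartile range spans about 20 to 27 days (for example 22 to 42 days late at 2 SD) and more at 1 SD (12 to 48). With 30% of days missing the 2-SD median is still 34. Reading the earliest change point in place of the dominant one gives 12 to 13 days (28-day ramp), 17 to 22 (56-day) and 20 to 29 (84-day) at autocorrelation 0.30.

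**Step 3: stage attribution.** Let the ramp start at the Start Conversation (day 18), with the Insight Conversation on day 46 and a total of 1.4 or 2 SD. Among series with a detection, the dominant change point falls on or after the Insight Conversation in roughly 60% for a 56-day ramp and roughly 80 to 85% for an 84-day ramp. A 28-day ramp is seldom misplaced (1 to 6%), and a true step in about 1% or fewer.

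**Step 4: steady drift.** A straight drift of total D over 130 days, split at any day b, has segment means centred at b/2 and (b + 130)/2. These are 65 days apart, so the phase means differ by D × 65/130 = D/2. A drift of 1.4 SD therefore gives 0.7 SD, above the 0.3 that Table 1 says the PDT can detect, and the series can pass the gate. WBS with independent errors then reports a change point in 48% of series (D = 1.0 SD) and 84% (D = 1.4 SD), against 14% for a flat series.

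**Step 5: the statement that WBS is free of assumptions.** At the protocol's own autocorrelation of 0.30, with the usual difference-based noise estimate, C = 1.3 and no correction, a series with no change gives at least one change point in about 84% of runs, against 14% with independent errors.

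**Step 6: does a slope-capable model help?** A flat-then-linear fit dates the 84-day ramp at a median of 0 to 0.5 days after onset (2 to 3 SD, autocorrelation 0.30). At 1 SD the median is +4.5 days (interquartile range −19 to +25), so it is nearly unbiased but imprecise. The same single kink dates a 28-day ramp with a plateau about 23 days too early, because that shape has two kinks.

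**The case against.** The best defence is that the article names a procedure and a reference but no contrast, threshold or software, and that an analysis plan not shown here might use a variant that handles slopes. That would excuse silence. It does not make the printed sentence true of the method it names.

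Other objections do stand and limit the point.

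- A reader might infer that every gradual change is dated about a month late. The documents give no ramp length, and that delay needs improvement spread over about 8 to 12 weeks. Shorter ramps are off by 1 to 3 weeks.
- A reader might infer that RQ3 will manufacture the hypothesised four-week lag of fatigue behind FSE. That needs FSE to jump, fatigue to climb over 8 to 12 weeks, and both to start on the same day. Two outcomes that climb at a similar pace shift together. Even in the favourable case (1.4 SD, rising to the end of the series) only about 33% of first change points fall within 7 days of the four-week mark. A false lag is possible but not predicted.
- A reader might infer that the wrong stage is always credited. A change starting at the Insight Conversation and dated 4 to 5 weeks late still lies in the Experiment Period. Misattribution arises when a slow change starts in the Measurement Period.
- RQ2 says that ITSA helps to judge whether a level change reflects a trend. This is a partial guard against drift, although RQ3 does not make a date conditional on it.
- The single-case work is framed as exploratory. RQ1 uses the randomisation test, and RQ4 defines responders by the PDT.

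**Conclusion.** The statement that WBS gives the moment of slope change is wrong as written, and so is the statement that it has no assumptions. For gradual change the date falls part-way up the ramp: about 1 week late for a 2-week ramp, 2 weeks for 4, 3 weeks for 6, and 4 to 5 weeks for 8 to 12, with wide scatter for individual participants. If the earliest change point is read, the delay for 8 to 12 weeks is about 2.5 to 4 weeks. These figures rest on linear ramps, standard mean-shift WBS and an assumed threshold. The direction of the error does not depend on the threshold, since it already appears without noise.

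The harm is confined to RQ3: onset dates, attribution to stages, and comparison of timing across outcomes. This should be corrected, but it does not threaten the trial's group-level conclusion.

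**What to change.** - Limit the WBS statement to level changes, and drop the claims that the moment is exact and that the method is assumption-free.
- For series with an ITSA slope change, date the onset with a piecewise-linear change-point method that allows more than one kink and accounts for autocorrelation. A single kink is not enough, because it misdates a ramp that levels off.
- Choose between step, piecewise-linear and straight-line fits by a criterion set in advance. Apply the ITSA trend result before any change-point date is interpreted, so that a steady drift is not given one.
- Report each date with an interval, and compare dates across outcomes only with those intervals.

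The cost is a change of wording and one further routine on data already being collected. The drawback is that intervals for gradual change will be wide (an interquartile range of about 26 days for a one-kink fit to a 1.4-SD ramp with independent errors), so fewer participants will have a sharp date, and choosing between fits adds a selection step for each series.

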#### RQ4: Which characteristics are predictive of changes in the study outcomes during the Booster intervention?

To explore participants’ characteristics that may predict changes in outcomes (see section “Objectives”), multiple analyses are planned. First, a multi-level analysis will be used to study the relation between self-reported goal attainment and changes in outcomes. Second, participants will be grouped into responders and non-responders based on a significant difference in FSE with the PDT (RQ2). We will describe and compare the (baseline) characteristics of responders versus non-responders (e.g. baseline FSE and fatigue, duration of symptoms, school absence, and illness identity), using the Mann–Whitney *U* test for continuous predictors, and a Fisher’s Exact Test for categorical data.

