### Sample size {14}

The power to detect an intervention effect with a multiple baseline design (RQ1) depends on the autocorrelation of consecutive daily progress monitor measurements, the start moment range, the number of repeated measurements, the intervention effect, and the number of cases [52]. In the earlier PROfeel study [48], the median autocorrelation of weekly measurements was 0.17 for FSE, 0.30 for fatigue severity, and 0.09 for QoL. Median autocorrelation of the five times daily ESM item on fatigue severity was 0.37 [48]. We expect the daily measurements in this study to show a higher autocorrelation than weekly measurements, but lower than a five times daily item. Thus, we assumed the autocorrelation in our study to be 0.30 across outcomes. The start moment range is nine, as the Booster intervention is randomised to start (T1) ten to eighteen days after the start of the daily progress monitor (T0). With 100% compliance, the number of repeated measurements is 130. With the abovementioned assumptions and inclusion of twenty cases, with up to 30% of daily measurements missing, the multiple baseline single-case randomisation test (SCRT) can detect medium to large intervention effects of ≥ 0.7 with a power of ≥ 0.80 at the group level (RQ1, Table 1). However, we anticipate small intervention effects since Booster is an early intervention, not treatment. The SCRT, used in SCED, has limited power to detect such small intervention effects [37, 52, 53]. In contrast, the permutation distancing test (PTD), developed for testing differences in means in single-case observational designs (SCODs), exhibits higher statistical power [53]. It is important to note that SCOD cannot establish causality. With the abovementioned assumptions, with up to 40% of daily measurements missing, the study is well powered to observe changes in outcomes for effect sizes as small as 0.3 at the single-case observational level (RQ2, Table 1).

**Table 1 Tab1:** Power for detecting intervention effects at the group and single-case level

Factors influencing power	Study design	
Autocorrelation (%)	30	
Repeated measurements (*n*)	130	
Power (%)	≥ 80	
Cases (*n*)	20 (group level)	1 (single-case)
Test	Multiple baseline SCRT	PDT
Start moment range (*n*)	9	NA
Maximum percentage missing data to retain sufficient power (%)	30	40
Minimum detectable effect size	0.7 (medium to large)	0.3 (small)

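### RQ4 looks for predictors by splitting participants on a direction-free significance verdict; at the small effects expected, that label is mostly chance, and the split discards power that the continuous FSE change would keep

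*Protocol article*

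**What the plan says.** The Objectives section puts RQ4 under the secondary objective and asks whether "baseline participant characteristics are predictive of improvements during the Booster intervention (RQ4"; that question has a direction. The RQ4 statistical section plans two analyses. A multi-level model relates self-reported goal attainment to outcome change. For the other characteristics (for example baseline FSE and fatigue, symptom duration, school absence, illness identity), "participants will be grouped into responders and non-responders based on a significant difference in FSE with the PDT (RQ2", and the groups are compared by Mann–Whitney U or Fisher's exact test.

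The RQ2 section uses the same labels, for the PDT and ITSA taken together: "identifying which individuals show significant change in outcomes in Phase B (responders) and which do not (non-responders". On the test itself it says: "The PDT will test the null hypothesis that observations within one individual are evenly distributed between Phase A and B". It names the mean level change as the PDT's test statistic. None of these places gives a direction, a minimum size of change or an alpha.

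The Sample size section expects small effects. It nevertheless claims, for as much as 40% missing diary data, that "the study is well powered to observe changes in outcomes for effect sizes as small as 0.3 at the single-case observational level".

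**The concern.** Whether a single-case test reaches significance depends on the size of that person's change, on day-to-day noise, on the number of completed diaries and on chance. Where single-case power is low, chance dominates, and two people with the same true change often land in different groups. The plan then treats the groups as a measure of response and compares 20 people across the split, although the PDT already yields a signed level change for each of them.

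The multi-level model is described for goal attainment only, so the search for baseline predictors rests on this label. The Discussion presents the study as showing for whom Booster works. A label that is mostly chance would hide true predictors. One without direction could also put people whose FSE fell among the responders.

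**Working it through.** **1. Single-case power: the plan's own figure first.** Table 1 gives at least 80% power at effect size 0.3. Inputs from Sample size: "With 100% compliance, the number of repeated measurements is 130"; "we assumed the autocorrelation in our study to be 0.30 across outcomes"; up to 40% missing. Phase A is taken as 42 days and Phase B as 130 − 42 = 88. Assumed, because not stated: alpha 5%, both one- and two-sided, and 0.3 read as a difference in units of the within-person SD.

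Generous ceiling, ignoring autocorrelation, complete data: SE = √(1/42 + 1/88) = 0.188 and 0.3/0.188 = 1.60. Two-sided power ≈ Φ(1.60 − 1.96) = 36%; one-sided Φ(1.60 − 1.645) = 48%. The best possible split (65/65) gives 40% and 53%.

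With autocorrelation 0.30, by generalised least squares with Σij = 0.30^|i−j| and SE² the phase element of (X′Σ⁻¹X)⁻¹:

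| Missing | SE | 0.3/SE | Power two-/one-sided | Effect for 80% power, two-/one-sided |
|---|---|---|---|---|
| 0% | 0.252 | 1.19 | 22% / 33% | 0.71 / 0.63 |
| 40% | 0.291 | 1.03 | 18% / 27% | 0.82 / 0.72 |

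This is close to the best a valid mean-shift test can do. An approximate distance-permutation test built from the RQ2 description gave 14% and 22% with complete data. The stated 80% at 0.3 was not reached under any variant. If everyone truly gained 0.3 SD, two thirds or more would be labelled non-responders.

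**2. What the label is made of.** Assumed: true effects normal with mean 0.3 to 0.7 and between-person SD 0.2 to 0.5; missingness uniform from 0 to 60%; two-sided 5% verdict.

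- True effect: 17 to 49% of label variance (17 to 42% at mean 0.3).
- Compliance: 0.4 to 1.5%, and at most 2.4% when everyone has the same true effect.
- Chance: the remaining 50 to 82% (57 to 82% at mean 0.3).
- Significant worsening: 0 to 7% of participants. In the worst case (mean 0.3, SD 0.5) this is 0.069/0.397 = 17% of those labelled responders.

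**3. Cost of splitting.** Twenty people, 0 to 40% missing, and a baseline characteristic correlated r with the true effect. Entries are power at 5%: Mann–Whitney on the direction-free label, Mann–Whitney on a label counting only improvements (two-sided significance with a positive sign), and Spearman on the estimated change.

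| Mean | SD | r | Direction-free | Improvement only | Continuous |
|---|---|---|---|---|---|
| 0.3 | 0.3 | 0.5 | 0.162 | 0.196 | 0.322 |
| 0.3 | 0.5 | 0.5 | 0.131 | 0.275 | 0.445 |
| 0.3 | 0.5 | 0.7 | 0.253 | 0.579 | 0.809 |
| 0.5 | 0.3 | 0.7 | 0.410 | 0.443 | 0.630 |
| 0.5 | 0.5 | 0.9 | 0.709 | 0.903 | 0.985 |
| 0.7 | 0.5 | 0.9 | 0.790 | 0.872 | 0.981 |

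Over all 18 combinations (means 0.3, 0.5, 0.7; SD 0.3, 0.5; r 0.5, 0.7, 0.9), the direction-free label keeps from 0.131/0.445 = 29% to 0.790/0.981 = 81% of the continuous analysis's power. That is a loss of about 20 to 70%. At mean 0.3 it keeps 29 to 54%. The improvement-only label keeps from 0.196/0.322 = 61% to 0.903/0.985 = 92%, a loss of about 10 to 40%. A middle case (SD 0.4, r = 0.6) gives 0.22 to 0.34, 0.35 to 0.39 and 0.56 to 0.59 respectively. A rerun of the SEs and of the 18 combinations agreed within simulation error.

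**The case against.** Several points on the other side have weight.

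- **RQ4 is secondary and exploratory.** This is true, and it limits the severity. Even the continuous analysis has only 32 to 47% power at r = 0.5, so the change improves RQ4 without making it well powered.
- **Direction may be settled elsewhere.** A reader might infer that the plan counts significant declines as response. The text does not say so: it leaves direction open, the objective speaks of improvements, and sidedness may stand in an analysis plan that is not shown. What remains is a wording gap between the objective and the grouping rule.
- **Compliance.** A reader might infer that the label largely measures diary completion, so that predictors of compliance would pass as predictors of response. The numbers do not support this. With compliance itself as the tested characteristic, Mann–Whitney flagged it in 4.6 to 6.2% of simulated trials, roughly the nominal 5%. Compliance does move the responder rate when effects are large: at a common effect of 0.7 it is 78% with under 10% missing and 58% with over 50% missing.
- **Size of the loss.** A loss of about half fits small effects with a direction-free label. It is not a general figure.
- **A common 0.3 gain leaves nothing to predict.** This is correct; that case only illustrates misclassification. The comparison in step 3 lets true effects vary between people.
- **Proxy test.** The power figures come from a mean-shift test, not the PDT software, and from one reading of the effect-size scale. The permutation approximation gave lower power, not higher.

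**Conclusion.** The point holds, as a moderate one. The baseline-predictor analysis is fixed on a significance verdict without direction or size, in a setting where the anticipated effects give single-case power of about 18 to 33% at 0.3 SD. The label then mostly reflects chance, with compliance a minor contributor. Splitting on it loses power in every scenario tried: about 20 to 70%, or about 10 to 40% if response is restricted to improvement.

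The single-case power rests on the protocol's 130 measurements and autocorrelation of 0.30, and on an assumed alpha, split and effect-size scale. The label make-up and power losses also rest on assumed mean effects, between-person SDs, missingness and predictor correlations; the protocol gives none of these for RQ4, hence the ranges.

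**What to change.** Make each participant's signed FSE level change, in raw VAS units and with its standard error, the RQ4 outcome. Raw units are preferable because dividing by each person's own SD would again make equal changes look different in people with noisier days. Relate the change to baseline characteristics by Spearman correlation, or by a phase-by-characteristic interaction in a multilevel model. The interaction model also takes categorical characteristics and extends the model type already planned for goal attainment.

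Keep the responder split as description only. Define a responder as someone with a significant improvement in FSE, and use the same definition in RQ2 and RQ4. State that RQ4 has limited power at 20 participants.

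The cost is a change of wording and slight extra analysis work. The level change is already the PDT's test statistic, and no new data are needed.
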